## Abstract

**Background:**

Effective teamwork and sufficient communication are critical components essential to patient safety in today’s specialized and complex healthcare services. Team training is important for an improved efficiency in inter-professional teamwork within hospitals, however the scientific rigor of studies must be strengthen and more research is required to compare studies across samples, settings and countries. The aims of the study are to translate and validate teamwork questionnaires and investigate healthcare personnel’s perception of teamwork in hospitals (Part 1). Further to explore the impact of an inter-professional teamwork intervention in a surgical ward on structure, process and outcome (Part 2).

**Methods:**

To address the aims, a descriptive, and explorative design (Part 1), and a quasi-experimental interventional design will be applied (Part 2). The study will be carried out in five different hospitals (A-E) in three hospital trusts in Norway. Frontline healthcare personnel in Hospitals A and B, from both acute and non-acute departments, will be invited to respond to three Norwegian translated teamwork questionnaires (Part 1). An inter-professional teamwork intervention in line with the TeamSTEPPS recommend Model of Change will be implemented in a surgical ward at Hospital C. All physicians, registered nurses and assistant nurses in the intervention ward and two control wards (Hospitals D and E) will be invited to to survey their perception of teamwork, team decision making, safety culture and attitude towards teamwork before intervention and after six and 12 months. Adult patients admitted to the intervention surgical unit will be invited to survey their perception of quality of care during their hospital stay before intervention and after six and 12 month. Moreover, anonymous patient registry data from local registers and data from patients’ medical records will be collected (Part 2).

**Discussion:**

This study will help to understand the impact of an inter-professional teamwork intervention in a surgical ward and contribute to promote healthcare personnel’s team competences with an opportunity to achieve changes in work processes and patient safety.

**Trial registration:**

Trial registration number (TRN) is ISRCTN13997367. The study was registered retrospectively with registration date 30.05.2017.

## Background

On the basis of international studies, the World Health Organization (WHO) estimates that between 3 and 16% of all patients treated in hospitals are affected by adverse events [1]. Poor teamwork is an independent cause of many of the system failures that lead to patient harm [2–4], which are considered as preventable [5, 6]. Despite improvements in the past 15 years, patient safety remains an important public health concern [7]. Effective teamwork and good communication are critical components essential to patient safety in today’s specialized and complex healthcare services [3, 8, 9]. A focus on teamwork competencies in complex healthcare systems such as leadership and coordination are identified by the WHO as a priority for research on patient safety in the Western world [10]. Teamwork is described in terms of behaviour, cognitions and attitudes that make interdependent performance possible [11], which is defined as: “The interaction or relationship of two or more health professionals who work interdependently to provide care for patients” ([12], p. 3). Teamwork is one of six core competencies seen as necessary for health professionals to master in order to meet the current and future demands for the quality of care [13].

Hospital units are representing frontline microsystems in hospitals where patients and healthcare professionals meet, and where care quality, patient safety and clinical outcomes are being produced [14]. These microsystems have the greatest opportunity to develop and improve work processes [15]. An extensive review of factors associated with team performance has identified shared mental models, mutual respect and trust, and closed-loop communication as the underpinning conditions required for effective teams [16]. However, various challenges exist within the frontline healthcare environment. For example, there are different perceptions and expectations of the roles and collaboration in teams among healthcare professionals [17, 18]. Moreover, studies have also demonstrated a variation in their perception of patient safety culture [19, 20], while another challenge to effective teamwork is the hierarchical structure among healthcare personnel [21, 22]. The association between adverse events and insufficient teamwork have been known for some time, but it is only in recent years that an evidence-based understanding of the problem has been developed, as well as an efficient programme to promote patient safety. Furthermore, it has been demonstrated that team training can improve efficiency in inter-professional teamwork within hospitals [23–26]. Team training is recommended for those who are expected to work together in teams [27], which requires that health-care personnel across professions should train together. Although there is an increasing awareness regarding teamwork competencies, healthcare has implemented team training in healthcare education and clinical practice to a small extent [28–30]. Team Strategies and Tools to Enhance Performance and Patient Safety (TeamSTEPPS®) [31] is an evidence-based teamwork system based on research on teamwork, team training and cultural change [16, 32, 33]. The teamwork system is released from the US Agency for Healthcare Research and Quality (AHRQ) and the Department of Defense as a national team training programme. TeamSTEPPS provides tools, strategies and measurements to promote team practice in all aspects of healthcare [34], and with the use of an implementation strategy based on Kotter’s model of organizational change [35].

### Theoretical framework

The Systems Engineering Initiative for Patient Safety 2.0 model (SEIPS 2.0) [36, 37], a framework developed from a human factors perspective for patient safety, will be used as a theoretical framework for this research project on teamwork in hospital. Human factors is a discipline concerned with the understanding of the interaction between humans and other elements of a system. According to Health and Safety Executive [38], human factors refer to: environmental, organizational and job factors, and human and individual characteristics which influence behaviour at work in a way that can affect health and safety. The general structure of the SEIPS 2.0 model includes the work system, which produces work processes, which in turn shapes the outcomes [36]. Frontline healthcare personnel are doing their work in an inter-professional patient care team in the centre of a complex work system in which structural factors such as practical tasks/procedures, equipment and technology, physical environment and organization affect their teamwork, and thus the results related to safety and quality in patient care [39]. A human factor-based healthcare system redesign with the SEIPS model is found in a systematic review [40] as a useful approach for improving patient safety and quality of care.

### Rationale for the research project

Since the majority of patient medical treatment and care takes place in inter-professional teams, the quality of the teamwork is a key feature of patient safety. Despite previous research shows that interventions focusing on inter-professional team training promote the quality of professional practice, there are still little knowledge about its impact on hospitals wards. Most research on teamwork and team training has been conducted in operating rooms, intensive care and emergency rooms. Furthermore, most research on teamwork has been conducted in the United States, but less in European and Scandinavian. This study “Teamwork in hospitals” will be conducted in hospital wards among frontline healthcare personnel in Norway. The patient care teams within these units consist of inter-professionals team members with a common goal and responsibility for a defined groups of patients.

### Aim

The aims of this study are to translate and validate teamwork questionnaires and investigate healthcare personnel’s perception of teamwork in hospitals (Part 1), and to explore the impact of an inter-professional teamwork intervention in a surgical ward on structure, process and outcome (Part 2).

## Methods/design

### Design

In order to address the aims of the study, a descriptive, explorative and a quasi-experimental interventional design will be applied. The study comprises six sub-studies and an overview of the specifics aims, designs and methods is shown in Table 1.

**Table 1 Tab1:** Overview of the six sub-studies, aims, designs and methods

	Part 1		Part 2			
	Study 1	Study 2	Study 3	Study 4	Study 5	Study 6
Aims	To translate questionnaires into Norwegian and to analyse the questionnaire’s psychometric properties.	To investigate healthcare personnel’s perception of teamwork and team decision making, and attitude towards teamwork.	To explore the impact of an inter-professional teamwork intervention in a surgical ward with regard to team decision making, patient safety culture and teamwork.	To describe inter-professional team members’ and leaders’ perception of teamwork and the impact of implementation of a teamwork intervention in a surgical ward.	To explore patients’ perception of quality of care in relation to an inter-professional teamwork intervention in a surgical ward.	To explore the impact of an inter-professional teamwork intervention in a surgical ward with regard to patient outcome and adverse events.
Design	Cross-sectional	Cross-sectional	Quasi-experimental – controlled before-and- after.	Qualitative descriptive	Quasi-experimental – uncontrolled before-and-after.	Quasi-experimental – time-series
Intervention			Six hours of inter-professional team training and implementation of tools and strategies in a surgical ward.			
Sample/Setting	Healthcare personnel, approximately 600, working in acute and non-acute units in Hospital A and Hospital B.	Healthcare personnel, approximately 600, working in acute and non-acute units in Hospital A and Hospital B.	All healthcare personnel, approximately 120, working in three surgical wards in three hospitals, including one intervention ward (Hospital C) and two control wards (Hospital D and Hospital E).	Leaders, physicians, registered nurses and assistant nurses, approximately 20, working in the intervention surgical ward in Hospital C.	Patients admitted to the intervention surgical ward (Hospital C) who meet the inclusion criteria: 18 years or older, understand Norwegian, are in a mental and physical health condition which makes it ethically justifiable to participate. Power analysis is conducted.	Patient register data and data from patients’ medical records (Hospital C). A power analysis with regard to number of patients’ medical records is conducted.
Data collection	Translation and back-translation of the three questionnaires: Teamwork Perceptions Questionnaire (T-TPQ), Teamwork Attitude Questionnaire (T-TAQ), Collaboration and Satisfaction About Care Decisions (CSACD). A survey with a paper version of the translated questionnaires.	A survey with a paper version of the translated questionnaires T-TAQ, T-TPQ, CSACD.	An electronic survey with T-TAQ, T-TPQ, CSACD and HSOPSC questionnaires will be administered at three occasions (before the intervention, and after six and 12 months). Ward statistics will be collected.	Focus group interviews will be conducted on three occasions (before the intervention, and after six and 12 months).	A survey with paper version of the questionnaire Quality from Patient’s Perspective will be administered on three occasions (before the intervention and after six and 12 months).	Anonymous patient data from local registers and from medical records (by use of Global Trigger Tool) will be released before and during the intervention period.
Data analysis	IBM SPSS 23 with descriptive statistics, explorative factor analysis and IBM SPSS AMOS 22 with confirmatory factor analysis. Intraclass Correlation (ICC) and Cronbach’s alpha	IBM SPSS 23 with descriptive statistics, Chi-square test, Mann-Whitney U-test, Kruskal-Wallis test, t-test, ANOVA and Multiple regression analysis.	IBM SPSS 23 with descriptive statistics, Chi-Square test, Mann-Whitney U-test, Kruskal-Wallis test, Paired t-test, Wilcoxon Signed rank test, ANOVA and Multiple regression analysis.	A Manifest inductive content analysis.	IBM SPSS 23 with descriptive statistics, Chi-Square test, Mann-Whitney U-tests, Kruskal-Wallis test, ANOVA and Multiple regression analysis.	IBM SPSS 23 with descriptive statistics, Time series analysis. Chi-Square test, Mann-Whitney U-tests, Kruskal-Wallis tests, ANOVA and Multiple regression analysis.

### Research setting

The study will be carried out in five different hospitals (Hospital A, B, C, D, E) in one hospital trust in Norway, and will represent both acute and non-acute departments. Hospital A is represented with internal medicine, gynaecology, obstetrics, surgery, emergency room, intensive care, operating rooms and anaesthesia, and Hospital B with internal medicine (Part 1). Hospital C is represented with a surgical intervention ward and Hospital D and Hospital E with one surgical control ward each (Part 2).

### Sample and data collection

#### Healthcare professionals

The target population is frontline healthcare personnel.

In part 1, all physicians (110), registered nurses (405), assistant nurses (59), midwives (24), physiotherapists (19) and occupational therapists (7) will be invited as respondents. Three Norwegian translated questionnaires measuring teamwork will be tested for psychometric properties, and healthcare personnel’s perception of teamwork, team decision-making and attitude towards teamwork will be investigated. A paper-based version of the Teamwork Perceptions Questionnaire (T-TPQ) [41], Teamwork Attitude Questionnaire (T-TAQ) [42], Collaboration and Satisfaction About Care Decisions (CSACD) [43] and questions on sociodemographic and educational background will be administered to the frontline healthcare personnel.

In part 2, all physicians, registered nurses and assistant nurses in an intervention ward and two control wards will be invited as respondents to explore the impact of an inter-professional teamwork intervention in a surgical ward with regard to team decision-making, patient safety culture and teamwork. An electronic survey with the Norwegian translated questionnaires T-TPQ [41], CSACD [43], T-TAQ [42], Hospital Survey on Patient Safety Culture (HSOPSC) [44] and data on sociodemographic and educational background will be administered to the frontline healthcare personnel before intervention, and after six and 12 months. Focus group interviews with physicians (*n* = 5), registered nurses (*n* = 5), assistant nurses (*n* = 5) and leaders (*n* = 4) in the surgical intervention ward will be conducted before intervention, and after six and 12 months, to explore their perception of teamwork and the impact of the inter-professional teamwork intervention within the ward.

#### Patients

In part 2, patients admitted to the intervention surgical ward who meet the inclusion criteria: being 18 years or older, understand Norwegian, as well as being in a mental and physical health condition that makes it ethically justifiable to participate, will be invited to explore their perception of quality of care during their hospital stay. A paper version of the questionnaire Quality from Patient’s Perspective (QPP) [45] will be administered to the patients before the intervention, and after six and 12 months. Patient size calculation was estimated by power analysis. To detect a mean difference of 0.4 (the primary endpoint) of the item “participation in medical treatment” a sample size of 65 (baseline), 80 (after 6 months) and 80 (after 12 months) (alpha <.05, power 0.80, standard deviation of 0.9) would be needed to find a significant difference between groups.

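### With the printed inputs, the patient-survey sizes of 65, 80 and 80 give power of about 0.75, not 0.80, for each comparison with baseline

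*Protocol article*

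**What the plan says.** The sample size for the patient survey is in the protocol article under Methods/design, Sample and data collection, Patients. The target is given as "To detect a mean difference of 0.4 (the primary endpoint) of the item" on participation in medical treatment. The sizes and the other inputs are given as "a sample size of 65 (baseline), 80 (after 6 months) and 80 (after 12 months) (alpha <.05, power 0.80, standard deviation of 0.9"). These numbers "would be needed to find a significant difference between groups".

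The section does not state sidedness, the test, which groups are compared, or why baseline is smaller than the follow-up waves. Table 1 describes Study 5 as "Quasi-experimental – uncontrolled before-and-after". The tests it lists for Study 5 include Mann-Whitney, Kruskal-Wallis, ANOVA and multiple regression. No paired test appears there, although Study 3 has two.

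**The concern.** A before-and-after study measures change from baseline, so both comparisons that bear on the intervention use the group of 65. The standard two-sample calculation with the printed difference and standard deviation gives 80 per group. The plan has 80 only in the two follow-up waves. The printed power would then hold for 6 against 12 months, which says nothing about change from before the intervention.

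At stake is the accuracy of the stated power for the only endpoint that the article labels primary. The chance of missing a true difference of 0.4 would be about 25%, where the text implies 20%.

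**Working it through.** **Inputs** (all from the Patients section unless noted)
- Mean difference 0.4 and SD 0.9, so the standardised difference is 0.4/0.9 = 0.444.
- Alpha 0.05, two-sided by assumption: z = 1.960.
- Power 0.80: z = 0.842.
- Groups of 65, 80 and 80, treated as independent because Table 1 lists no paired test for Study 5.

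**Step 1. Reproduce the plan's figures with equal groups.**
n per group = 2 × (1.960 + 0.842)² × (0.9/0.4)² = 2 × 7.85 × 5.0625 = 79.5, rounded up to 80. The t test gives 80.4. The two figures of 80 reproduce; the 65 does not.

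**Step 2. Power for 65 against 80.**
- SE = 0.9 × √(1/65 + 1/80) = 0.9 × 0.1670 = 0.1503.
- 0.4/0.1503 = 2.66.
- Power = Φ(2.66 − 1.96) = Φ(0.70) = 0.759. The noncentral t gives 0.753.

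**Step 3. Power for 80 against 80 (6 v 12 months).**
SE = 0.9 × √(2/80) = 0.1423; 0.4/0.1423 = 2.81; power = Φ(0.85) = 0.803. The noncentral t gives 0.798.

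**Step 4. Difference detectable with power 0.80, 65 against 80.**
0.1503 × (1.960 + 0.842) = 0.421 (0.424 by t test).

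**Step 5. Sizes that would give 0.80 (t test).**
With 80 at follow-up, baseline needs 81. With 65 at baseline, each follow-up wave needs 106.

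**Step 6. Other readings that might explain 0.80.**

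| Reading | Power |
|---|---|
| One-sided 0.05, 65 v 80 | 0.84 |
| Mann-Whitney, 65 v 80 (assumed efficiency 0.955) | 0.74 |
| Contrast using the pooled three-group error (222 df) | 0.755 |
| Bonferroni for two comparisons with baseline | 0.65 |
| Three-group F test, means 0 / 0.4 / 0.4 | 0.77 |
| Three-group F test, means 0 / 0.2 / 0.4 | 0.66 |
| Three-group F test, one follow-up wave alone differs by 0.4 | 0.82 |

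A one-sided calculation with equal groups needs only 63 to 64 per group, so it cannot explain the 80. The 65 lies near the one-sided answer and the 80 at the two-sided one, but no single sidedness gives 0.80 for 65 against 80.

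**The case against.** Four points can be made for the plan.

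*Rounding.* The difference and SD are printed to one decimal. A difference of 0.42 would print as 0.4, and an SD of 0.85 would print as 0.9 and give 65 against 80 a power of 0.80. But rounding cuts both ways: an SD of 0.94 gives 0.716. Moreover, 80 is exactly the equal-group answer for 0.4 and 0.9 as printed. Rounding is possible but nothing in the text supports it.

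*The contrast is inferred.* The text speaks only of a difference between groups and names three of them, and Table 1 lists ANOVA and Kruskal-Wallis. It does not expressly promise 0.80 for each comparison with baseline. This stands, and it is a reason to name the contrast. It does not rescue the figure, because the F test exceeds 0.80 only if a single follow-up wave differs, a pattern that the Patients section does not describe.

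*An unseen derivation.* The Discussion says that each sub-study has its own protocol, and the reason for 65 may be given there. The figure can still be checked as printed, since every input but sidedness is on the page.

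*Weight.* A reader might infer that the patient survey is seriously underpowered, or that a null result would be badly misread. The documents do not support that. The shortfall is about 5 points of power on one item, the stated aim of Study 5 is exploratory, and the Data analysis plan provides for 95% confidence intervals where relevant. An interval shows what a null result excludes, whether planned power was 0.75 or 0.80.

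**Conclusion.** The stated power is wrong for the printed inputs. For either comparison with baseline it is about 0.75, and the difference detectable with power 0.80 is about 0.42, not 0.40. This rests on three assumptions: two-sided alpha of 0.05, independent samples at each wave, and the difference and SD taken as printed. None of the alternatives for a comparison with baseline in Step 6 yields 0.80.

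It is a modest error in a reported figure and worth correcting because the correction is simple. It is not a flaw in the design, and it changes no estimate, test or error rate.

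**What to change.** Restate the calculation in the Patients section, for example: with 65 patients at baseline and 80 at each follow-up, power to detect a mean difference of 0.4 (SD 0.9, two-sided alpha 0.05) is about 0.75 for each comparison with baseline, and the difference detectable with power 0.80 is about 0.42. If 65 was derived in some other way, add that derivation.

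Do not recover the power by switching to baseline against the two follow-up waves combined (65 v 160). That contrast gives 0.85 only if the full 0.4 is present at both waves. If the effect is 0.2 at 6 months and 0.4 at 12, the mean is 0.3, the SE is 0.9 × √(1/65 + 1/160) = 0.132, and power is about 0.62. According to Study status, the April and November 2016 surveys are already done, so the contrast would also be chosen after two of the three waves had been collected.

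The cost is a sentence or two and a slightly less favourable stated power. No extra patients are needed.

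### The sample size for the primary patient endpoint does not say which survey waves the 0.4 difference separates, and a single baseline v follow-up comparison (65 v 80) has about 75% power, not 80%

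*Protocol article*

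**What the plan says.** Under Patients, the article designates a primary endpoint and gives its power inputs: "To detect a mean difference of 0.4 (the primary endpoint") on one item of the Quality from Patient's Perspective questionnaire, with "alpha <.05, power 0.80, standard deviation of 0.9". The resulting numbers are "a sample size of 65 (baseline), 80 (after 6 months) and 80 (after 12 months"), which "would be needed to find a significant difference between groups". The questionnaire "will be administered to the patients before the intervention, and after six and 12 months", in the intervention ward only.

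Table 1 lists for Study 5, after descriptive statistics, "Chi-Square test, Mann-Whitney U-tests, Kruskal-Wallis test, ANOVA and Multiple regression analysis". The Data analysis plan adds hypothesis tests and/or generalized linear models and generalized estimating equations for comparisons over time, with 95% confidence intervals where relevant. None of these methods is tied to the primary endpoint.

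Under Study status, the April and November 2016 surveys are done and the June 2017 survey is still to come.

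**The concern.** A power figure belongs to a particular comparison. Here there is one difference, one SD, one alpha and one power, but three groups, and the text says only that the difference is between groups. It could mean baseline v 6 months, baseline v 12 months, baseline v both follow-ups pooled, 6 v 12 months, or a global test across all three waves. These have different power at 65/80/80, so the stated 80% may not describe the comparison that is eventually reported.

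The next subsection, on medical records, does name its comparison (baseline v the implementation period), so the article can be this specific in the space it has.

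Two things are at stake. The reader cannot tell whether the survey was large enough for the comparison that measures the intervention. And because two of the three waves were already collected when the article was written, the choice of contrast could be made after seeing part of the data.

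**Working it through.** **Inputs.** Difference 0.4, SD 0.9, alpha 0.05, power 0.80 and wave sizes 65/80/80 are all from the Patients section. Three assumptions are added: two-sided testing (sidedness is not stated), a common SD at all waves, and different patients at each wave. The last is inferred: Table 1 lists paired tests for Study 3 but none for Study 5, and patients rate their own hospital stay.

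**Reproducing the plan's figure.** For two equal groups, n per group = 2(1.960 + 0.842)² × 0.9² / 0.4² = 2 × 7.85 × 5.0625 ≈ 79.5, so 80 (81 with the t distribution). The two figures of 80 are therefore the answer to a two-sided, two-group question. The 65 does not come out of it. Keeping the 65:80 ratio, 80% power would need 73 v 90.

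**Power of each possible two-group contrast.** SE = 0.9 × √(1/n₁ + 1/n₂), and power ≈ Φ(0.4/SE − 1.960). The noncentral t result is in the last column.

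| Contrast | n | SE | 0.4/SE | Power (normal) | Power (t) |
|---|---|---|---|---|---|
| Baseline v 6 months, or baseline v 12 months | 65 v 80 | 0.1503 | 2.662 | 0.759 | 0.753 |
| 6 v 12 months | 80 v 80 | 0.1423 | 2.811 | 0.803 | 0.798 |
| Baseline v pooled follow-up | 65 v 160 | 0.1324 | 3.022 | 0.856 | 0.853 |

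The only pair of single waves that reaches about 80% is the one with no pre-intervention patients.

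**Omnibus ANOVA at 65/80/80.** Noncentral F with 2 and 222 degrees of freedom, λ = Σnᵢ(μᵢ − μ̄)²/0.81:
- means 0/0.4/0.4: λ = 7.396/0.81 = 9.13, power 0.771
- means 0/0.2/0.4: λ = 5.76/0.81 = 7.11, power 0.656
- means 0/0/0.4: λ = 8.249/0.81 = 10.18, power 0.817

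**Error rate if pairs are tested uncorrected.** The two baseline contrasts share the baseline group, so they are correlated: (1/65)/(1/65 + 1/80) = 0.55. Simulating three null wave means (2,000,000 draws), with each test at two-sided 0.05 and any significant result counted, gives 8.9% for the two baseline contrasts and 12.2% for all three pairs. Bonferroni correction would restore 5% but lower the 65 v 80 power from 0.753 to 0.654 (two contrasts) or 0.595 (three).

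**One-sided reading.** One-sided testing gives 63 per group and 84.5% power for 65 v 80. It does not give 80 per group, so it fits the stated numbers less well.

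**The case against.** The strongest reply is that this is a condensed article. Which contrast is primary, which listed test applies and how alpha is shared are commonly settled in a fuller document. The Discussion says that each sub-study has its own protocol, and Study 5's aim is worded as exploratory. That disposes of any complaint that the article merely omits an analysis rule or a multiplicity procedure. It does not dispose of the sample-size statement, which claims 80% power for numbers that do not give it for either single baseline v follow-up comparison. The exploratory aim lowers the weight of multiplicity, but the article itself chose a primary endpoint with an alpha and a power.

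Two stronger readings are tempting, and the article does not support them.

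- A reader might infer that the 5% error rate is lost. It is lost only if pairwise tests are each run at 5% and any one counts as success. No section states that rule, and the listed omnibus tests, or one named contrast, keep 5%.
- A reader might infer that the listed analyses cannot return a mean difference comparable with 0.4. That is true of the rank tests and of an omnibus p-value. But Table 1 also lists multiple regression, and the Data analysis plan lists generalized linear models and estimating equations; a regression on wave gives exactly that estimate with its interval.

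It is also fair to say that 80% is met under some readings: baseline v pooled follow-up (0.853), or the omnibus test if the whole change appears at one follow-up (0.817).

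**Conclusion.** The point stands in limited form. The article states 80% power for the primary patient endpoint without identifying the comparison. At the planned sizes the figure runs from about 66% to 85% across the uncorrected readings above. For the most direct one, baseline against a single follow-up, it is about 75%, roughly 5 percentage points short. That shortfall comes from the baseline group of 65 and exists before any multiplicity correction. The 9% or 12% error rate is a conditional risk that the wording leaves open, not a property of the plan.

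These results rest on two-sided testing, a common SD of 0.9, independent patients across waves, and the planned sizes; the article does not report how many patients actually responded.

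**What to change.** Before the June 2017 wave is analysed:

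1. Name one baseline v follow-up contrast as primary, at two-sided 0.05. Baseline v 12 months is one example. Nothing in the article makes it the only defensible choice; what matters is that one is fixed.
2. Estimate it as a mean difference with a 95% confidence interval, using the regression already listed for Study 5, with wave as the explanatory variable. The article names no patient covariates collected with the questionnaire, so adjustment should be specified only if such variables exist at every wave compared.
3. Report the other contrasts, the rank tests and the omnibus tests as secondary.
4. Restate the power for 65 v 80 as about 75%.

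The cost is wording only: no new data and no new method. The downside is that the other follow-up comparison loses confirmatory status and the stated power becomes slightly less favourable.
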